**INTRODUCTION**

The Weight-bearing in Ankle Fractures (WAX) trial is an NIHR Research for Patient Benefit (RfPB) study that will randomise patients to weight-bear early (at two-weeks postoperatively) or wait till six weeks postoperatively, which is the current standard of care.^1,2^ It will also conduct health economic analysis to determine the cost-effectiveness of the two weight-bearing strategies.

Recent qualitative studies have highlighted the burden for patients having to endure a period of non-weight bearing.^3,4^ While they often report difficulty with non-weight-bearing, it is not known how patients respond once permitted to weight-bear.  Even if instructed to weight-bear, many patients are wary of pain, falls and reinjury and so avoid walking on their ankle for several weeks.^4^

We do not know how patients decide what is an acceptable level of discomfort when starting to weight-bear (whether this is undertaken early or late) or how they decide to stop using their post-operative splints or walking aids.  There is little guidance for clinicians on advising patients and no rehabilitation package for patients themselves.

An intervention to encourage weight-bearing would be considered a “complex intervention”.^5^ This is because techniques to change weight-bearing behaviour would include several interacting components, which may be related to those delivering (healthcare professionals) and those receiving the intervention (patients).^5^ Behaviour change theory has been used to design and evaluate similarly complex rehabilitation interventions in chronic musculoskeletal conditions.^6^ This framework allows the linkage of determinants of behaviour (e.g. pain beliefs or resource availability) to behaviour change techniques, which can be used to develop an intervention.^7^

**We therefore propose:**

Co-production of a rehabilitation package to facilitate safe weight-bearing after ankle fracture surgery based on the behaviour change wheel.

# STUDY DESIGN

This Study Within a Trial (SWAT) has three work packages:

1. An embedded exploratory study investigating the impact of adverse pain beliefs in patients with surgically managed ankle fracture.
2. Conduct an analysis of interviews of patients and healthcare professionals participating in the WAX trial. This analysis will investigate patients’ experience of pain, recovery and commencing weight-bearing.
3. Co-design a rehabilitation package to facilitate weight-bearing after ankle fracture surgery, based on the behaviour change wheel. This will be through a series of workshops with healthcare professionals and patients.

# METHODOLOGY

## Study Participants

- Patients having undergone operative fixation of an unstable ankle fracture that have been approached to take part in the WAX trial
- Healthcare professionals that have been involved in the WAX trial.

## Recruitment

Recruitment will be embedded in the WAX trial recruitment process.

Separate consent forms allow patients who decline participation in the WAX trial to be invited for interviews and workshops to ensure the qualitative study is maximally representative of an ankle fracture population

Additionally, patients, carers and healthcare professionals will be recruited through professional and charitable societies including Arbeitsgemeinschaft für Osteosynthesefragen (AO)UK, the Orthopaedic Trauma Society and through local Patient and Public Involvement (PPI) networks and those of existing patient representatives.

## Consent

As part of the initial consent discussion for the WAX trial, patients will be asked whether they may be approached about participating in interviews and workshops. Prior to interview, participants will receive written and verbal information about participating in an interview. Participants who agree to be approached will have a separate informed consent discussion for the interviews with a member of the research team either in person, or by phone. NHS staff will initially be invited to interview by phone or email, and if they agree to be approached, an informed consent discussion will take place with a researcher from the WAX office by phone, videocall or in person.

# SWAT PROCEDURES

The study will follow the Medical Research Council framework for developing and evaluating complex interventions^5^:

- Identify the evidence base (Completed pre-RAAFT)
- Identify/ develop theory (work package 1 and 2)
- Model process/ outcomes (work package 3)

**Work package 1: An embedded exploratory study investigating the impact of adverse pain beliefs**

Baseline characteristics and variables for linear regression models:

Additional patient characteristics are embedded into the baseline demographic data collection in the WAX trial. They include:

- Educational attainment
- The Charlson comorbidity index
- The Index of Multiple Deprivations (IMD)

Two short questionnaires will explore participants’ pain beliefs:

**Fear of movement**: The Tampa Scale for Kinesiophobia -11 is a brief, reliable, and valid measure of fear of movement/(re)injury for patients with chronic painful conditions.^8^

**Pain self-efficacy**: The pain self-efficacy questionnaire-2 is a validated, abbreviated measure of an individual’s confidence in their ability to accomplish tasks, overcome problems and live a normal life despite pain.^9^

The other predictor variables already collected as part of the WAX trial include age, gender, occupation (sedentary vs manual labour), injury mechanism and blinded weight-bearing allocation.

Outcome Measurements

The primary outcome measure for the exploratory analysis is the Olerud and Molander Ankle Score (OMAS) measured at 4 months post-randomisation. It is a reliable and valid ankle-specific patient-reported outcome measure used in several other ankle fracture studies. ^10–12,13^.

The secondary outcome measures are Health-related quality-of-life (EQ-5D-5L) and Adverse events (AEs).

Sample size/ available data:

The sample size for the WAX trial is 436 patients, with a predicted 10% loss to follow-up rate. With 10 predictor variables, 80% power and a significance level of 0.05, the regression model would be able to detect and account for 4% of the variability in OMAS at 4 months (F^2^=0.042 = R^2^=0.040; calculations performed using G*Power3.1.9.4). This R^2^ is much lower than the expected adjusted R^2^ based on previous studies.^14,15^

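### The only power figure in work package 1 is for the whole ten-predictor model, so its 80% does not transfer to the pain-belief question in the work package's title

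*Protocol*

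**What the plan says.** The Study Design section describes work package 1 as "An embedded exploratory study investigating the impact of adverse pain beliefs in patients with surgically managed ankle fracture". The procedures section for that work package measures pain beliefs with two questionnaires, the TSK-11 and the PSEQ-2. It lists eight further predictors: education, Charlson index, deprivation, age, gender, occupation, injury mechanism and weight-bearing allocation.

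The paragraph on sample size and available data starts from the parent trial: "The sample size for the WAX trial is 436 patients, with a predicted 10% loss to follow-up rate". It continues "With 10 predictor variables, 80% power and a significance level of 0.05", and concludes that "the regression model would be able to detect and account for 4% of the variability in OMAS at 4 months", with the detail "F^2^=0.042 = R^2^=0.040; calculations performed using G*Power3.1.9.4". It then supports the 4% by a comparison: "This R^2^ is much lower than the expected adjusted R^2^ based on previous studies". The expected value is not given.

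The Analysis section for work package 1 tests candidate variables one at a time, enters the significant ones into a multiple regression, and includes the pre-injury value of the outcome. It names no test of the model as a whole. No detectable effect is given for the TSK-11 or PSEQ-2, singly or together.

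**The concern.** A power figure is useful when it belongs to the test that answers the question. Here the test behind the figure asks whether any of ten predictors is related to OMAS at 4 months. The titled question is whether pain beliefs are. Age, comorbidity or injury mechanism could bring the model to 4% with nothing from the TSK-11 or PSEQ-2. The analysis also enters pre-injury OMAS, which is not among the ten and could add more.

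The supporting comparison has the same limitation. The expected adjusted R² reads as a whole-model quantity, so it speaks to how well the full model may predict and not to what pain beliefs add.

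What is at stake is interpretation. Work package 1 feeds the design of the rehabilitation package. If neither score shows an association, the stated 80% gives no basis for judging whether a worthwhile association could have been missed.

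**Working it through.** **Inputs from the protocol (work package 1, sample size paragraph).** 436 patients; 10% loss, so 436 × 0.9 = 392.4, taken as N = 392; 10 predictors; α = 0.05; power 0.80; f² = 0.042, R² = 0.040.

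**Method.** Fixed-model multiple regression with p predictors, of which u are tested. Power = P[F′(u, N − p − 1; λ) > F crit], where F′ is noncentral F and λ = f²N. For the whole model f² = R²/(1 − R²). For a subset, partial f² = ΔR²/(1 − R² of the full model).

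**Step 1: reproduce the stated figure.** Whole model, u = p = 10, denominator df = 392 − 11 = 381.
- 80% power needs f² = 0.0424, that is R² = 0.0424/1.0424 = 0.0407.
- At f² = 0.042, λ = 0.042 × 392 = 16.5 and power is 79.5%. Power reaches 80.0% at N = 396 and is 84.6% at N = 436.

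The stated figure is thus the whole-model test after 10% loss, to rounding.

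**Step 2: rule out the partial tests.** Same model, N = 392, 80% power:

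| Test | Detectable partial f² | Partial R² = f²/(1 + f²) |
|---|---|---|
| One score, u = 1 | 0.0201 | 2.0% |
| Both scores, u = 2 | 0.0248 | 2.4% |

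Neither is near 0.042.

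**Step 3: what a whole-model R² implies for the two scores.** Assume ten uncorrelated predictors sharing R² equally, so that both scores add 0.2R² and one adds 0.1R². The protocol does not give its expected R², so a range is shown (N = 392).

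| Whole-model R² | Joint partial f² = 0.2R²/(1 − R²) | Joint power (2 df) | Single-score power (1 df) |
|---|---|---|---|
| 4% | 0.008/0.96 = 0.0083 | 34% | 25% |
| 10% | 0.020/0.90 = 0.0222 | 75% | 55% |
| 15% | 0.030/0.85 = 0.0353 | 92% | 75% |
| 20% | 0.040/0.80 = 0.0500 | 98% | 88% |

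At the other extreme, if the whole 4% came from pain beliefs, f² = 0.04/0.96 = 0.0417. Power is then 96% for the joint test, or 98% if a single score carried it all.

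**Step 4: the figure that fits the question.** With partial f² = 0.0248 and other predictors explaining R²c, the detectable increase is ΔR² = (1 − R²c) × 0.0248/1.0248:
- R²c = 0: 2.4%
- R²c = 10%: 2.2%
- R²c = 20%: 1.9%
- R²c = 30%: 1.7%

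Adding pre-injury OMAS (p = 11), or allowing 25 model df for multi-category predictors, leaves the joint partial f² at 0.0248 and the single-score value at 0.0201.

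**The case against.** The sentence names the regression model and never claims 80% power for the TSK-11 or PSEQ-2. The Analysis section aims at all candidate variables and does not single out two as tested and eight as adjusters. The work package is called exploratory throughout, its sample size is fixed by the parent trial, and the paragraph reads as a feasibility check on the data that will be available. The low power figures need a model that explains only 4%, whereas the protocol says this "is much lower than the expected adjusted" R². At an equal f² of 0.042, a 1-df or 2-df test has 98% or 96% power, more than the whole-model test.

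Most of this stands, and it limits the point. A reader might infer that the pain-belief question is underpowered, or that the stated figure tells us nothing. The documents support neither inference. With about 392 patients an increase of roughly 2% in explained variance is detectable, and 34% or 25% power arises only if the model explains exactly 4%, equally shared. A reader might also infer that the protocol promises 80% power for pain beliefs; it does not.

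What remains is that the only figure given belongs to a test that is neither the titled aim nor a described analysis. The advantage of fewer degrees of freedom cannot be used either, because no partial effect for pain beliefs is stated. Whether the cited earlier studies report whole-model R² cannot be checked here; that is simply how the comparison reads.

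**Conclusion.** The point holds as a mismatch between the power figure and the question. The stated f² = 0.042 is the 10-df whole-model value at about 392 analysed. It leaves joint power for the two pain-belief scores anywhere from 34% to 96% in the two cases worked at R² = 4%, and still lower if the scores contribute less than an equal share. The relevant detectable effects are a partial f² of about 0.025 for both scores and 0.020 for one, so a correct statement is somewhat more favourable than the one printed.

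These figures assume 10% loss, α = 0.05 without multiplicity adjustment, and a model fixed in advance. The equal-sharing powers also assume uncorrelated predictors. None of the calculations reflects univariate screening or multiple imputation. Materiality is modest: the work package is exploratory, and no shortage of patients is shown.

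**What to change.** 1. State that 4% is the variance explained by the whole ten-predictor model.
2. Add that about 392 analysed patients give 80% power for a partial f² of about 0.025 for TSK-11 and PSEQ-2 jointly (an R² increase of about 2.4% to 1.7% when the other predictors explain 0 to 30%), and of about 0.020 for one score.
3. Do not offer the comparison with earlier R² values as support for the pain-belief question.
4. Report, as the key exploratory analysis for 4-month OMAS, the joint 2-df test of the two scores added to the listed covariates and pre-injury OMAS. Keep both scores in the model whatever the univariate screen shows.

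The cost is two reworded sentences, one added nested-model test, and fixing the covariates for that test in advance instead of letting the screen choose them. No more patients are needed, and the analysis stays exploratory.

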## Work package 2: Qualitative interviews

### Semi-structured interviews with patients

Participants’ experiences of treatment and barriers and facilitators to commencing weight-bearing after ankle fracture surgery will be explored. Participants will be invited to take part in an interview at around 8 weeks after their surgery. Interviews will be up to 60 minutes and conducted by telephone or videocall. All interviews will be audio-recorded, anonymised and transcribed verbatim. Interviews will be semi-structured and use a brief, flexible topic guide.

Maximum variation sampling strategy to ensure the spread of patient characteristics by age (age over or under 60), and pain self-efficacy (scores higher or lower than eight based on mean results from previous studies^14,15^). Participant interviews will continue until data saturation is achieved. Based on a previous study, it is estimated data saturation will be achieved in around 25-30 interviews. ^4^

### Semi-structured Interviews with surgeons and healthcare professionals

25-30 Healthcare professionals, including surgeons, physiotherapists and research nurses will be sampled to reflect the multidisciplinary care team delivering care and research interventions to patients after ankle fracture. They will be invited to an interview to discuss their perceptions of how patients make sense of current weight-bearing instructions and any common difficulties they express.

##

**Work package 3: Iterative co-design of a rehabilitation package to facilitate safe weight-bearing**

Informed by work package 1 and 2, a rehabilitation strategy will be co-designed, using the three phases of the Behaviour Change Wheel (BCW). This technique is informed by extensive theory and has been used to design and implement rehabilitation interventions.^7^ The three phases are:

1. *Understand the behaviour* by assessing participants’ capability, opportunity and motivation (COM-B) to engage with the behaviour (weight-bearing). These will be derived from the qualitative interviews. These will then be mapped to the 9 intervention functions of the Behaviour Change Wheel.^7^ A set of candidate behavioural change intervention bundles will then be generated.
2. *Understand intervention options* using the APEASE (affordability, practicability, effectiveness/ cost-effectiveness, acceptability, safety/ side effects and equity) criteria.^16^

Workshop 1. The formulated behaviour change intervention bundles (likely 3-5 options) will be presented to a workshop of 7-12 patients and carers. A maximum variation sample of patients from different demographic and socio-economic backgrounds will be recruited.

Workshop 2. The intervention bundles (likely 2-3 refined from workshop 1) will be presented to surgeons, physiotherapists and other healthcare professionals (7-12 in total).

Nominal Group Technique will be used to structure the discussions and prioritise the intervention bundles.

1. *Understand the content and implementation options* using the Template for Intervention Description and Replication (TiDieR) checklist.^17^

The 1-2 intervention bundles prioritised from workshops 1-2 will be explored. Candidate behavioural change techniques (BCTs) derived from the BCT Taxonomy v1 (BCTTv1)^18^ will be selected and incorporated into the intervention bundles.

Workshop 3. All stakeholders from workshops 1 and 2 will be invited to a combined workshop to discuss the selected 1-2 intervention bundles. Using the TiDieR checklist, we will discuss the where, when, how and by whom the interventions could be delivered.

The techniques will be refined to formulate a coherent rehabilitation package. Stakeholders that consent to further contact will be invited to contribute and comment on this process.

Workshops will be conducted face-to-face, virtually via videoconference, or a combination of both. The workshop frequency, duration and format may be amended to cater for participants preferences and availability according to social distancing guidelines in place at the time.

## Discontinuation/Withdrawal of Participants from Study

Each participant has the right to withdraw from the study at any time. All workshops will be audio-record, transcribed and anonymised. If a participant of the workshop meeting withdraws then it may not be possible to withdraw their data as well as it will constitute a part of the flow of workshops and removing it will leave subsequent elements of the discussion out of context.

# ANALYSIS

# Work package 1: Exploratory Analysis

Standard descriptive summaries for patient baseline characteristics and outcome values will be reported. Multiple imputation methods will be used to impute missing data using missing at random assumptions.^19^ To test whether the candidate variables are predictors of outcome, univariate linear regression model analyses for continuous outcomes and logistic regression for binary outcomes will be used. Variables significantly associated with outcomes will be entered into multiple regression models. Three models will be generated with OMAS, EQ5D5L and adverse events as the dependent variable and pre-injury values of the outcome measure and candidate predictors will be entered as independent variables.

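### Univariable significance screening decides which predictors enter the work package 1 regressions; it does not match the ten-predictor power calculation and can drop or distort the pain-belief estimates

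*Protocol*

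**What the plan says.** The Protocol describes work package 1 under Study Design as "An embedded exploratory study investigating the impact of adverse pain beliefs in patients with surgically managed ankle fracture". The measures of interest are TSK-11 and PSEQ-2: "Two short questionnaires will explore participants’ pain beliefs".

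The section Work package 1: Exploratory Analysis gives the modelling rule in three steps:

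- Screening: each candidate is tested alone, by linear regression when the outcome is continuous and by logistic regression when it is binary.
- Entry: "Variables significantly associated with outcomes will be entered into multiple regression models".
- Final models, one each for OMAS, EQ-5D-5L and adverse events: "pre-injury values of the outcome measure and candidate predictors will be entered as independent variables".

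The sample-size paragraph of the work package 1 procedures starts from the parent trial: "The sample size for the WAX trial is 436 patients, with a predicted 10% loss to follow-up rate". It then works "With 10 predictor variables, 80% power and a significance level of 0.05", and reports a detectable f² of 0.042 (R² of 0.040) for OMAS at 4 months.

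**The concern.** The work package asks what pain beliefs do to outcome, yet the entry rule lets the data decide whether the pain-belief measures appear in the adjusted model and what they are adjusted for. Three things follow.

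1. A pain-belief measure or a confounder can fail the screen because a correlated predictor hides its crude association. It is then lost from the adjusted analysis, or the remaining coefficients go under-adjusted.
2. A weak or null predictor that passes has passed partly because its estimate was large by chance. The same data then supply the reported coefficient and interval, and no shrinkage or validation step is described.
3. The power statement concerns ten predictors entered together, whereas the entry rule yields a model of unknown size and content.

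The third step of the rule also sits awkwardly with the second. It speaks of candidate predictors being entered without saying whether that means all of them or only those that passed.

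**Working it through.** **Inputs from the Protocol.** N = 436 × 0.90 = 392.4, taken as 392. Power 80%, α = 0.05. The work package 1 procedures list ten candidates: educational attainment, Charlson index, IMD, TSK-11, PSEQ-2, age, gender, occupation, injury mechanism and allocation.

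**Assumptions.** The Protocol gives no entry threshold, effect sizes or correlations. I take a two-sided 0.05 screen and standardised predictors, and vary the rest.

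**Step 1: the Protocol's own figure.** Omnibus F test with 10 and 392 − 11 = 381 df, noncentrality λ = f² × N = 0.042 × 392 = 16.46. Power is 79.5%. Solving for 80% gives f² = 0.0424, and R² = 0.0424/1.0424 = 0.041. The stated figure reproduces, and it does so for a model holding all ten predictors.

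**Step 2: why passing variables are overstated.** The screen passes a variable only if its observed correlation exceeds t/√(df + t²) = 1.966/√(390 + 3.865) = 0.099 in absolute value. A predictor whose true effect is 0.05 therefore passes only when its sample correlation is at least about twice the truth.

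**Step 3: why masked variables are lost.** With standardised predictors, the crude slope is β₁ + rβ₂. For β₁ = 0.15, β₂ = 0.30 and r = −0.5 it is 0.15 − 0.15 = 0, so the variable passes at about the 5% error rate of the screen although its adjusted effect is real.

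**Step 4: simulation** (N = 392, ten predictors, screen then least squares on the survivors; at least 4,000 runs per row; paired values are repeat runs).

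| Scenario for the pain-belief measure | Passes screen | Mean estimate if selected | 95% CI coverage if selected | Full model detects |
|---|---|---|---|---|
| β = 0.05, independent | 16–17% | 0.124 | 83–85% | 16% |
| β = 0.10, independent | 50% | 0.139 | 95% | 49% |
| β = 0.15, independent | 85% | 0.164 | 98% | 84% |
| β = 0.20, independent | 98% | 0.20 | 97% | 97–98% |
| β = 0, r = 0.5 with a covariate of 0.1 | 16% | 0.073–0.075 | 73–75% | 5% |
| β = 0.15, r = −0.5 with a covariate of 0.3 | 4–5% | 0.144–0.146 | 46–54% | 75–76% |

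The full model was unbiased, with coverage close to 95% in every scenario.

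**Step 5: sensitivity to the assumed correlations.** Take TSK–PSEQ −0.45, age–Charlson 0.45, an age effect of −0.12 and a PSEQ-2 effect of 0.2. Power for TSK-11, screened against full:

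| Age–TSK correlation | TSK-11 effect −0.10 | TSK-11 effect −0.15 |
|---|---|---|
| −0.2 | 39% v 46% | 73% v 79% |
| 0 | 50% v 50% | 83% v 82% |
| +0.2 | 48% v 43% | 81% v 79% |

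Across TSK-11 effects of −0.10 to −0.30, coverage when selected was 92–96% at −0.2 and 94–96% at 0 and +0.2.

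**Step 6: can the data carry the full model?** Ten predictors plus the pre-injury score leave 392 − 12 = 380 residual df, counting one df per predictor. The detectable R² moves from 0.041 to 0.042. In the ten-predictor model a single coefficient is detectable at a partial R² of about 0.020.

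**The case against.** The work package is labelled exploratory, sets no decision threshold and does not touch the WAX treatment comparison. The capability, opportunity and motivation inputs to the co-design come from the interviews, so no work package 1 p-value decides anything. This stands, and it limits the severity.

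The 0.05 entry level is assumed, and a looser level in an SAP would change every screening figure. The last sentence of the rule can also be read as entering every candidate, which would agree with the power calculation. Both points stand. They make the mismatch something to reconcile rather than a flat contradiction, but the screening sentence would still need to change.

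Two stronger readings are tempting. A reader might infer that screening creates a false-positive problem, since 1 − 0.95¹⁰ = 40% of null analyses pass at least one variable, or 1 − 0.95³⁰ = 79% over three outcomes. That is the multiplicity of ten tests, and the unscreened model shares it: 39% of null runs had at least one p < 0.05. The 79% further needs independent outcomes, whereas all three come from the same patients. For a single independent null coefficient, unconditional rejection after screening was 4.7%, so it is not inflated.

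A reader might also infer that the pain-belief intervals are invalid across the board. The tables do not support this. Poor coverage is confined to null, very weak or confounded predictors that happen to be selected, and the TSK-11 power loss disappears or reverses when the assumed age–TSK correlation is 0 or +0.2.

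**Conclusion.** The concern holds in a limited form and should be fixed. The Protocol states a significance-based entry rule that protects neither the two measures the work package is about nor the allocation, and its power statement describes a different model. The possible harm is loss of masked predictors and overstatement of weak ones. It ranges from practically nothing (independent effects of 0.2 or more) to severe (a masked effect of 0.15, almost always dropped). Where this study falls in that range cannot be known from the Protocol, since it gives no effects or correlations. For the two continuous outcomes the sample supports the full model, so screening gains little. For adverse events no event rate is given, and it cannot be checked whether ten predictors are supportable.

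**What to change.** **OMAS and EQ-5D-5L.** Replace the screening sentence with wording such as: *For each outcome one prespecified linear model will be fitted, containing TSK-11, PSEQ-2, the other eight listed candidates and the pre-injury value of the outcome, with no data-driven selection. Estimates will be pooled over the imputed datasets, and all coefficients will be reported with 95% confidence intervals. Univariable results are descriptive only.* The final sentence of the section should then say explicitly that all candidates are entered, which also brings it into line with the power calculation.

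**Adverse events.** Always retain TSK-11 and PSEQ-2, and prespecify a covariate set that the number of events can support, or use penalised regression, instead of significance screening.

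**Cost.** One paragraph of text and no new data. The linear models use about 11 df out of about 392 patients, slightly more if educational attainment or injury mechanism has several categories, and intervals will be slightly wider than in a smaller model.

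### One screened-regression rule covers all three outcomes: for adverse events its pre-injury term cannot exist, and its significance screen exaggerates the odds ratios that are kept, seriously so if events are rare

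*Protocol*

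**What the plan says.** Protocol, ANALYSIS, Work package 1: Exploratory Analysis. Candidates are first tested one at a time: "univariate linear regression model analyses for continuous outcomes and logistic regression for binary outcomes will be used". Those that are significant go forward to multiple regression. Then "Three models will be generated with OMAS, EQ5D5L and adverse events as the dependent variable", and in the same sentence "pre-injury values of the outcome measure and candidate predictors will be entered as independent variables". No exception is made for adverse events.

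Protocol, SWAT PROCEDURES, Work package 1. OMAS at 4 months is the primary outcome; EQ-5D-5L and adverse events are secondary. The candidates are educational attainment, Charlson index, IMD, TSK-11, PSEQ-2, and "age, gender, occupation (sedentary vs manual labour), injury mechanism and blinded weight-bearing allocation", which makes 5 + 5 = 10. On size, the protocol starts from the parent trial's 436 patients less 10% lost, allows 10 predictors at 80% power and a 0.05 level, and concludes that "the regression model would be able to detect and account for 4% of the variability in OMAS at 4 months". Nothing comparable is said for adverse events, and no event frequency is given.

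**The concern.** There are three separate difficulties, and none causes another.

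- **The pre-injury term.** OMAS and EQ-5D-5L can be recalled for the time before the fracture. An adverse event after fracture surgery has no such value, so the sentence prescribes a covariate that cannot be collected.
- **The size argument.** The 4% figure is for an F test in a linear model on all patients followed up. In a logistic model the information comes from the number of events, so the figure gives no assurance for adverse events.
- **The screen.** If a variable enters only when its univariable test is significant, the coefficients that survive are those that happened to come out large. The fewer the events, the larger an estimate must be to pass, and the greater the exaggeration.

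At stake is the size of any reported association between pain beliefs and adverse events. Work package 3 says that the rehabilitation package is informed by work packages 1 and 2, so an exaggerated association could carry undue weight there.

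**Working it through.** **1. The protocol's own figure.** Patients followed up: 436 × 0.9 = 392.4, about 392. For the overall F test with 10 and N − 11 degrees of freedom and noncentrality f² × N, 80% power at N = 392 needs f² = 0.0424, and R² = f²/(1 + f²) = 0.0407. At the stated f² = 0.042 the power is 79.5%. The protocol's 0.042 and 0.040 are reproduced. They concern OMAS only.

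**2. Events per candidate.** The event rate is an assumption. Events = 392 × rate, divided by 10 candidates:

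| Assumed rate | Events | Per candidate |
|---|---|---|
| 5% | 19.6 | 2.0 |
| 10% | 39.2 | 3.9 |
| 20% | 78.4 | 7.8 |
| 40% | 156.8 | 15.7 |

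Ten per candidate is reached at 100/392 = 25.5%. Counting one parameter per candidate is lenient if education or injury mechanism has more than two categories.

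**3. What the screen demands.** For a standardised predictor, the standard error of the univariable log-odds ratio is about 1/√(N·r·(1 − r)), where r is the event rate. At p < 0.05 (the protocol does not restate a threshold for the screen) the estimate must exceed 1.96 standard errors:

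| Rate | N·r·(1 − r) | SE | Smallest estimate that passes |
|---|---|---|---|
| 5% | 18.62 | 0.232 | 0.454 |
| 10% | 35.28 | 0.168 | 0.330 |
| 20% | 62.72 | 0.126 | 0.247 |
| 40% | 94.08 | 0.103 | 0.202 |

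Suppose the true value for TSK-11 is 0.3 per SD (an assumption). At 5% and 10% the bar lies above the truth, so every estimate that passes in the right direction overstates it.

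**4. Average size of what is kept.** For a normal estimate with mean 0.3 and standard error s, kept above bar c, the mean is 0.3 + s·φ(z)/(1 − Φ(z)), with z = (c − 0.3)/s. At 5%, z = 0.665 and the ratio is 1.26, giving 0.3 + 0.232 × 1.26 = 0.59. The other rates give about 0.45, 0.37 and 0.33.

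A simulation of the stated procedure agrees. It used N = 392, 10 independent normal candidates, true log-odds ratios of 0.3 for TSK-11 and −0.2 for PSEQ-2, and zero for the rest:

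| Rate | Mean retained log-OR (truth 0.3) | Ratio to truth | As OR (truth 1.35) |
|---|---|---|---|
| 5% | 0.61 | 2.0 | 1.84 |
| 10% | 0.46 | 1.5 | 1.58 |
| 20% | 0.38 | 1.3 | 1.46 |
| 40% | 0.34 | 1.1 | 1.40 |

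A repeat run gave 0.59, 0.46, 0.38 and 0.34. A second simulation with four true effects of 0.2 to 0.4 overstated the selected ones 1.97-, 1.55-, 1.24- and 1.15-fold at the same rates.

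**5. The alternative under the same assumptions.** A prespecified five-covariate Firth model, with no screen, averages about 0.29 to 0.30 for TSK-11 at every rate.

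**The case against.** **The analysis is exploratory and the outcome secondary.** This is fair. The protocol already labels the work exploratory, and powering only the primary outcome is normal. The definition, coding and expected frequency of adverse events may sit in a statistical analysis plan that is not shown, so their absence is no fault. What stands is that the protocol itself fixes the shared rule, including a term that one of its three models cannot contain.

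**The pre-injury term is a drafting slip.** Probably so: an analyst would leave it out and no estimate would change. It still needs correcting. A reader might infer that it drives overfitting; it does not, because a term that cannot be entered adds nothing to the model.

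**The model is bound to be badly overfitted.** A reader might infer this, but the protocol does not say that events are few. With a broad definition and a rate above about 25.5%, there are ten or more events per candidate. That the outcome is binary is also an inference, drawn from the provision for logistic regression when no other listed outcome could be binary.

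**Screening makes discrimination and calibration worse.** The calculations do not support this. With four true effects of 0.2 to 0.4, calibration slopes at 5, 10 and 20% were 0.40, 0.65 and 0.81 with the screen, against 0.40, 0.56 and 0.70 for the full ten-candidate model. Apparent AUC was lower with the screen (0.705 against 0.754 at 5%). No risk score is planned in any case. The harm from screening lies in the retained coefficients.

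**All candidates may enter.** The last sentence of the analysis text can be read so. Selection bias would then largely disappear (average inflation 1.00 to 1.08 at 5 to 40%), but events per candidate would stay as tabulated. The sentence before it says that significant variables are entered, and that is the reading used here.

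**Influence on the package is limited.** This is also fair. The behavioural content comes from the interviews, and no rule ties an odds ratio to it.

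**Conclusion.** The point holds in a bounded form. Two parts follow from the text alone: the adverse-event model is assigned a pre-injury covariate that cannot exist, and the sample-size statement does not extend to it. The third part is that the screen biases retained odds ratios away from the null. The direction is certain, but the size depends on an event rate that the protocol does not give. The overstatement of the log-odds ratio is roughly 1.5- to 2-fold at 5 to 10%, about 1.3-fold at 20% and about 1.1-fold at 40%.

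These sizes assume 392 patients, a yes/no outcome, a 0.05 threshold, independent standardised candidates and a true log-odds ratio of 0.3. Using all 436 patients changes little: at 10% there would be 43.6 events, or 4.4 per candidate. The documents do not support saying that the model will be badly overfitted.

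**What to change.** For the adverse-event model only:

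- Exempt it from the pre-injury covariate.
- Drop the significance screen.
- Fit one prespecified Firth or otherwise penalised logistic model with TSK-11, PSEQ-2 and a few fixed covariates already collected, for example age, Charlson index and allocation.
- Limit the number of parameters by the event count. Five parameters would have 19.6/5 = 3.9 events each at a 5% rate and 39.2/5 = 7.8 at 10%, so penalisation is still needed if events are rare.
- State in the protocol or the analysis plan that the 4% sample-size figure applies to OMAS alone.

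The cost is a change of wording, with no new data. The downside is that the remaining candidates are reported only descriptively for this secondary outcome.
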